### Recruitment

With support from clinical investigators, a Community Coordinator (CC) introduces the study to clinic staff at prospective recruitment sites and obtains permission to enroll from the facility head prior to beginning recruitment. The study asks clinic staff to approach all eligible women living with HIV registered for antenatal care, provide them with study information, and obtain their assent to be contacted by study staff.

Study staff visit the clinics weekly to obtain potential participant lists and contact them to confirm their eligibility, explain the purpose and procedures, and subsequently obtain informed consent for all study activities. Specifically, the CC meets with antenatal care (ANC) staff to arrange access to the ANC Register and to support identification of pregnant women meeting the eligibility criteria. Upon identification of potentially eligible women, the CC arranges for the health care worker to obtain assent to contact the mother directly. The CC begins direct engagement by reconfirming eligibility criteria are met—including the date of positive HIV test—prior to acquiring consent. With consent obtained, the study staff then completes the baseline assessment and discloses allocation to MME or TAU to the participant. Since this study focuses on the testing of intervention efficacy in a new context, we focus on recruiting into the MME group, and participants are placed into the control group based on overflow and availability (3:1). This also helps promote participant retention in the study.

Once the CC has identified a sufficient number of MME-allocated subjects within a cluster, study staff poll those participants to determine the week day suitable for the largest number of participants allocated to MME; the CC then makes a follow-up call to inform MME-assigned participants of the location, starting date, and anticipated end date of the group sessions. Sessions are scheduled to run at least once per week and may be scheduled twice per week if participants prefer, in order to maximize the possibility that all attendees benefit from all sessions of the intervention prior to delivery.

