### Condition assignment and blinding

Due to pragmatic challenges of recruiting pregnant women during the first 28 weeks of pregnancy, we are not able to use randomization. Participants who meet eligibility criteria are assigned by the research team to receive MME or TAU based on timing of recruitment (Fig. 2). Since we are not able to standardize the start of the intervention to the same week of pregnancy for participants, women are enrolled as long as it is feasible for them to complete eight sessions prior to week 36 of their pregnancy. In terms of blinding, participants and study staff administering the intervention are aware of treatment allocation; lead and senior investigators are blinded to treatment allocation. The biostatistician is not involved in the intervention assignment and is unblinded at the phase of analysis because the intervention group has measures immediately post-intervention that are not administered to the control group. Additionally, one of the primary analyses is to compare outcomes in the intervention group vs. the control group.

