**Covariates**				
Demographic measures	ALL	MME	ALL	N/A
Alcohol use (AUDIT)	ALL	MME	ALL	N/A
Sexual behavior (5 items)	ALL	MME	ALL	N/A
Intimate partner violence (WAST)	ALL	MME	ALL	N/A
**Qualitative** (open-ended; differs at each time points)	MME	MME	MME	N/A
**HIV metrics:** CD4 count and viral load (IDCC records/electronic medical record system)			ALL	1
**Birth outcomes:** birth weight, gestational age, APGAR scores (Delivery Summary Sheet)			ALL	1
**Infant health:** infant mortality, infant HIV status, feeding method, vaccinations, hospitalizations (dates, diagnosis) (“Under 5 Card”: asked from mother at 4 month follow-up)			ALL	1

1 Bivariate comparison of mean (median) scores at 16-week follow-up between intervention and control group

2 Bivariate comparison of change in mean (median) scores from baseline to 16-week follow-up between intervention and control groups

3 Bivariate comparison of mean (median) scores at baseline and post-MME within intervention group

4 Bivariate comparison of mean (median) scores at baseline and 16-week follow-up within intervention group

5 Bivariate comparison of mean (median) scores at post-MME and 16-week follow-up within intervention group

*ALL* all participants

*MME* only intervention participants

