### Covariates

Additional measures include sociodemographic information (date of birth and age; racial, ethnic, and/or tribal background; sex at birth and gender identity; sexual orientation; relationship status; highest education level; estimated total family income; employment pattern; money for basic necessities; assistance from government or local community leadership; membership in private medical aid; homelessness; and housing status, including household items). Three additional scales are included: (1) alcohol use via the 10-item Alcohol Use Disorder Identification Test (AUDIT) [96, 97]; (2) sexual behavior via five questions about number of sex partners in the past month; how often used condoms during sex with regular partner(s) in past month; how often used condoms with casual partners in past month; how often used condoms for paid sex in past month; and how often anal sex in past month; and (3) intimate partner violence via the 8-item Woman Abuse Screening Tool (WAST) [98]. These covariates will be collected at baseline and will be used in a purely descriptive fashion to characterize the sample.

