### Statistical analysis

We will examine baseline demographic characteristics of the intervention and control group and statistically test for differences between the groups on key characteristics to characterize the samples. Given the relative small sample size, nonparametric tests will be used to examine differences between groups. We will use bivariate analysis to compare primary outcomes of the mother’s reduced self-stigma, psychosocial outcomes, and treatment adherence, and secondary outcomes for infants including birthweight, timing of delivery, and developmental milestone between the treatment and control group using an intent-to-treat analysis at baseline and 4-month follow-up. Regarding missing data, we will conduct analyses based on complete data on each outcome and we will remove anyone if they do not have complete data for the outcome being assessed. Sensitivity analyses will be conducted based on the dose of intervention received using several different cut-points: (1) attended at least one session (yes/no), (2) number of sessions attended (count), (3) attended five or more sessions (yes/no), and (4) attended last session for graduation (yes/no). For bivariate tests, Wilcoxon rank-sum test will be used to examine differences in continuous variables between the intervention and control group. The chi-square test will be used for categorical data (Fisher’s exact test will be used when there are small cell counts). In addition, we will conduct exploratory analyses among intervention group participants in a pre/post-intervention analysis. Primary outcomes will be examined using the Wilcoxon signed-ranked test to examine difference among intervention participants from pre-intervention to post-intervention. Furthermore, we will examine whether there is correlation within groups and, if so, will then control for group membership in the analysis.

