Potential limitations of this study start with challenges in recruitment and retention. From the outset, difficulties in recruiting only primiparous women led us to expand our criteria to multiparous women. However, we can imagine women who have previously given birth may differ from those who have not. The challenges of rolling recruitment of pregnant women during the narrow window of eligibility of the first 28 weeks have also prevented us from randomizing the treatment and control groups; however, we are still allocating participants to groups systematically and will adjust for any baseline differences in analyses. Pregnant women have many competing demands on their time and so it can be challenging to participate in an 8-session program. We have been responsive to requests from groups that are interested in having sessions twice weekly. It would also be helpful to know which aspects of the interventions were most effective; however, since the components are integrated together, we will not be able to isolate the effects to specific components. Given the formative work and adaptation to this specific context, whether the findings themselves are generalizable must be empirically tested; however, the approach and standardized methods we have developed can be used to replicate the process in new settings. Finally, the child outcomes are exploratory, but if promising, then future studies should be powered to detect clinically meaningful differences in these variables.

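### Arms are formed without randomisation, yet every specified between-arm test is unadjusted; the Discussion promises an adjustment that no analysis section provides

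*Protocol article*

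**What the plan says.** **Assignment.** The Introduction says randomisation was not feasible and describes systematic assignment by the experimenter. Under Condition assignment and blinding, eligible women are "assigned by the research team to receive MME or TAU based on timing of recruitment". Under Recruitment, the focus is on filling MME and "participants are placed into the control group based on overflow and availability (3:1", that is, three MME to one TAU. These descriptions differ, and none is a fixed rule.

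**Between-arm tests.** Statistical analysis states: "We will use bivariate analysis to compare primary outcomes". For continuous outcomes the "Wilcoxon rank-sum test will be used to examine differences in continuous variables between the intervention and control group"; chi-square or Fisher's exact tests serve categorical ones. Table 1 gives two between-arm metrics. Metric 1 is a bivariate comparison of 16-week scores. Metric 2 is a "Bivariate comparison of change in mean (median) scores from baseline to 16-week follow-up between intervention and control groups".

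**Use of baseline data.** Statistical analysis will "statistically test for differences between the groups on key characteristics to characterize the samples". The Covariates section says its listed measures (sociodemographics, AUDIT, sexual behaviour, WAST) "will be used in a purely descriptive fashion to characterize the sample". The later regressions of outcome on arm are labelled exploratory and name no baseline covariate. The one adjustment named alongside the tests is for group membership, conditional on within-group correlation, which is a clustering matter.

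**The promise.** The Discussion concedes the lack of randomisation and says the team "will adjust for any baseline differences in analyses".

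**The concern.** Without randomisation, nothing in the design makes the arms comparable at baseline. Timing of recruitment could separate them on gestational age, since the start week is not standardised, and a loosely defined overflow rule could separate them on other things. Adjustment is the only remedy the protocol offers, and it appears only as a remark in the Discussion. The analysis section specifies unadjusted tests, and for the listed covariates the Covariates section says the opposite.

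The comparison matters to the study: Condition assignment and blinding calls MME versus control one of the primary analyses, significance is declared at p < 0.05, and a multisite trial proposal depends on this pilot's success. If the sections are followed as written, a difference that was there before the first session can be reported as an effect of MME.

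**Working it through.** The plan states no figure on this point, so there is none to reproduce. The check sets the passages side by side and then illustrates what is at stake.

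**Step 1: is there a place where the promised adjustment happens?**
- Rank-sum, chi-square and Fisher tests: no covariate.
- Table 1, metrics 1 and 2: both bivariate. Metric 2 uses the same outcome's baseline through subtraction.
- Baseline tests: for description only.
- Listed covariates: for description only.
- Regressions: exploratory; no baseline covariate named.

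So no analysis passage delivers the adjustment. For the listed covariates, the Covariates and Discussion sections cannot both be followed.

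**Step 2: inputs for an illustration.** From the protocol: two-sided alpha 0.05, 3:1 ratio, and the example size of 5 control and 15 intervention (Sample size and power). Assumed, because the protocol gives no value: baseline gap g = 0.5 SD, baseline-to-follow-up correlation r = 0.5 to 0.7, no treatment effect, and a second size of 10 control and 30 intervention.

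**Step 3: expected bias if the gap regresses toward a common mean.**
- Metric 1: r × g = 0.5 × 0.5 = 0.25 SD to 0.7 × 0.5 = 0.35 SD.
- Metric 2: (r − 1) × g = −0.5 × 0.5 = −0.25 SD to −0.3 × 0.5 = −0.15 SD. It over-corrects, in the opposite direction.
- Model adjusted for baseline: 0.

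These biases do not shrink as the sample grows.

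**Step 4: false-positive rates** (4,000 simulated trials per row, normal data, nominal 5%).

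| Control : MME | r | Metric 1 | Metric 2 | Baseline-adjusted |
|---|---|---|---|---|
| 5 : 15 | 0.5 | 6.7% | 6.3% | 5.0% |
| 5 : 15 | 0.7 | 8.4% | 5.7% | 5.1% |
| 10 : 30 | 0.5 | 9.6% | 8.8% | 4.7% |
| 10 : 30 | 0.7 | 14.5% | 7.7% | 5.2% |

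**Step 5: could baseline significance tests trigger the adjustment?** A rank-sum test would flag a 0.5 SD gap only about 12–13% of the time at 5 : 15 and about 25% at 10 : 30. Adjusting only for differences found by testing would usually miss it.

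**Step 6: the opposite assumption.** Suppose the gap is stable, at 0.5 SD at both times, with r = 0.6. The adjusted model is then biased by (1 − r) × g = 0.4 × 0.5 = 0.20 SD and rejects about 9–10% at 10 : 30. The change-score bias is 0 and it rejects about 5%. Neither method is right under both assumptions.

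**The case against.** The strongest reply has five parts.

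*The study is an exploratory pilot that discloses its lack of randomisation, and covariate choice usually belongs in an analysis plan.* This is fair as to detail, and the missing covariate list alone would be no finding. But an analysis plan could not honour both the Covariates and the Discussion sections; it would have to override one.

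*Metric 2 already uses baseline.* This stands. A reader might infer that the plan discards the baseline scores; it does not, for any stigma, psychosocial or adherence measure. Metric 2 still over-corrects when the gap regresses, and it ignores every other confounder.

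*The Covariates section does not forbid the useful adjustments.* This also stands. Its restriction covers only the measures it lists. Baseline outcome scores, gestational age and clinic cluster are not among them, and the exploratory regressions could hold them. They do not say so.

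*Bias in favour of MME is conjecture.* A reader might infer that women available for sessions are also the more adherent. The documents do not support this: Eligibility already excludes women who cannot attend from both arms, and availability is undefined and may refer to group places.

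*The inflation is small and the size is assumed.* At 5 : 15 it is indeed modest, and even that is only an example size. The 10 : 30 split is not in the protocol; its example of 40 belongs to a correlation.

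**Conclusion.** The concern holds as an inconsistency with consequences: assignment is non-random, the specified between-arm tests are unadjusted, and the promised adjustment has no place in the analysis.

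Its size cannot be read from the documents. Under the assumed regressing gap, the 16-week comparison is the more exposed, with an inflation that is modest at the example size and larger at 10 : 30. The change-score comparison is less affected. Baseline adjustment restores about 5% in that case but not if the gap is stable over time, so it should be the main analysis with the change score beside it, not presented as a cure. The direction of any bias is unknown, and no version removes unmeasured confounding.

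A reader might also infer that allocation must be changed for the remaining recruits. The documents do not require this, and it would mix two assignment mechanisms in one small study.

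**What to change.** 1. In Statistical analysis, for each outcome with a baseline measure, make the main between-arm analysis a short prespecified model of the 16-week score on arm and the same outcome's baseline value, adding gestational age at enrolment. Add clinic cluster only if the number of controls allows. Fit it whatever the baseline p-values.
2. Keep the rank-sum tests on the 16-week score and on change as supportive. Name the change-score result as a sensitivity analysis, because baseline adjustment is biased if the arm difference is stable over time.
3. For outcomes without a study baseline (CD4 count, viral load, birth and infant outcomes), label the comparisons as unadjusted for baseline and open to confounding.
4. Bring the Covariates section, the exploratory regression paragraph and the Discussion into line with this: say which baseline variables enter the model and which remain descriptive.
5. Give one consistent description of the assignment rule under Recruitment and under Condition assignment and blinding. No mid-trial change of allocation is needed.

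**Cost.** Wording only. The baseline scores are already planned, gestational age is needed to confirm eligibility, and clinic is known at recruitment. One or two covariates use degrees of freedom that are scarce with few controls, so the set must stay short. Unmeasured confounding remains and should be stated as a limitation.

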**Methods:**

This study will test MME against treatment as usual (TAU) among pregnant mothers diagnosed with HIV and their infants. Outcomes will be assessed during pregnancy and 16 weeks postpartum. Women who meet eligibility criteria are assigned to MME or TAU. Women assigned to MME are grouped with others with similar estimated delivery dates, completing up to eight intervention group sessions scheduled before week 36 of their pregnancies. Primary outcomes among mothers include (i) reducing self-stigma, which is hypothesized to mediate improvements in (ii) psychological outcomes (quality of life, depression and social functioning), and (iii) adherence to antenatal care and ART. We will also examine a set of follow-up infant birth outcomes (APGAR score, preterm delivery, mortality (at < 16 weeks), birth weight, vaccination record, and HIV status).

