This pilot study of MME collaborates with health clinics offering antenatal services under the Greater Gaborone District Health Management Team (GGDHMT) to conduct a pragmatic clinical trial [68, 69] of an innovative, culturally tailored stigma reduction intervention among pregnant mothers diagnosed with HIV. The intervention builds on prior evidence-based strategies while also integrating WMM for pregnant mothers in Botswana (see “Intervention rationale and components”). We named our intervention “MME” (pronounced “mm-eh”), short for “Mothers Moving towards Empowerment.” *Mme* is also a Setswana term used to address a respected woman. We utilize a pragmatic study design that retains all core elements except for randomization, which was not feasible among this complex population where we must group together women who are at approximately the same stage of pregnancy at the same time. Instead, we use systematic assignment by the experimenter to MME or a control group receiving treatment as usual (TAU). We measure primary and secondary outcomes at three time points (pre-intervention, immediately post-intervention, and at 16-week follow-up postpartum). All details regarding the protocol sections can be located through the SPIRIT checklist (Additional file 1).

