### Comparator: treatment as usual

Control participants receive TAU, including using free ART and antenatal services as they wish. Budget constraints do not allow us to implement a time and attention placebo control condition; this threat to validity in this pilot study will be accounted for in a future RCT. Control condition participants are assessed on all primary outcomes at the same time points as the intervention group (Fig. 2), except for immediately following intervention.

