### Assessments and outcome measures

All assessments are enumerated in Table 1, including their domain (name of the outcome), specific measurement, metric, method of aggregation, and time points. The three main time points are (1) baseline (< 28 weeks gestational age), post-intervention (immediately following completion of 8-session intervention, intervention group only), and follow-up (16 weeks postpartum). Primary outcomes for the mother include HIV stigma, psychosocial outcomes, treatment adherence, and HIV outcomes (e.g., viral load). Secondary outcomes for the infant include birth outcomes and early infant health. Stigma and psychosocial outcomes are collected via self-report questionnaires; all other outcomes are collected via health/medical records for the mother and infant. In addition, there are no additional studies using participants’ data and there are also no biological specimens that will be collected. If there are other studies to be conducted, there will be a separate procedure for additional consent.

**Table 1 Tab1:** Overview of measures

Assessment measure	Baseline (< 28 weeks gestational age)	Post-MME	Follow-up (16 weeks postpartum)	Comparison metric

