We will then build exploratory linear (continuous outcomes) or logistic (dichotomous outcomes) regression models to examine the effect of study arm on primary and secondary outcomes, and examine mediating effects of stigma on primary outcomes in mothers and exploratory outcomes in infants. We will prioritize objective measures in examining antenatal and ART outcomes and use self-report measures as a check on these findings. We will examine changes in predictors (e.g., stigma) between time points by creating difference variables and also examine these predictors as time-varying covariates in the regression model using generalized estimating equations (GEE) and structural equation models (SEM). A focus will be to examine whether changes in primary outcomes in mothers from baseline to post-intervention predict changes in primary outcomes at follow-up. If possible, SEM will also be used to examine structural relationships between latent constructs in the conceptual framework (e.g., among stigma subscales) and measured variables. Statistical significance will be assessed as *p* < 0.05. Statistical analysis will be conducted in Stata 16.

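### The only post-assignment stigma score shared by both arms is taken about 16 weeks or more after antenatal and birth outcomes, so it cannot be read as their mediator

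*Protocol article*

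**What the plan says.** The Methods part of the abstract makes the mechanism a hypothesis: "reducing self-stigma, which is hypothesized to mediate improvements in (ii) psychological outcomes", and it extends the same chain to antenatal and ART adherence. The Statistical analysis section then plans exploratory regression models for the effect of arm, and within them to "examine mediating effects of stigma on primary outcomes in mothers and exploratory outcomes in infants". It does not name the time point of the mediator and does not limit the outcomes to those that come after it. It also sets as a focus whether "changes in primary outcomes in mothers from baseline to post-intervention predict changes in primary outcomes at follow-up".

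On the schedule, the Comparator section says that TAU women are assessed when MME women are, "except for immediately following intervention". The Condition assignment and blinding section confirms that "the intervention group has measures immediately post-intervention that are not administered to the control group". The stigma rows of Table 1 (Berger scale, HCSS-B, Botho items) agree: all women at baseline, MME women only after the intervention, all women at 16 weeks postpartum.

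**The concern.** Reading stigma as the path from arm to outcome needs a stigma value in each arm that falls after assignment and before the outcome. The baseline score precedes the intervention, so it can be an adjustment variable but not a mediator. In TAU that leaves only the 16-week score, and several of the outcomes to be explained are settled by delivery.

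The risk is reverse causation. A preterm birth or a low birth weight could make a woman feel more stigma four months later. The model would then assign part of the arm effect to stigma even if stigma in pregnancy played no role. The Discussion says that the results will guide refinement of MME and preparation of a multisite RCT, so a mistaken statement about mechanism would be carried forward.

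**Working it through.** The plan gives no figure on this point to reproduce. The check sets the schedule against the outcomes and then illustrates the size of the possible error.

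**1. Calendar.** The Recruitment section places the 16-week postpartum visit at about week 56. Delivery is therefore taken at about week 56 − 16 = 40. Sessions are to finish before week 36, so the shared follow-up score comes about 56 − 36 = 20 weeks after that limit.

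**2. Stigma scores available (Table 1).**

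| Time | MME | TAU | Usable as a mediator of the arm effect? |
|---|---|---|---|
| Baseline | yes | yes | no, precedes the intervention |
| Post-intervention | yes | no | no, one arm only |
| 16 weeks postpartum | yes | yes | only for outcomes that come later |

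Using the post-intervention score for MME and the 16-week score for TAU would confound arm with time of measurement. Entering stigma as a time-varying covariate in GEE meets the same gap, because the middle wave exists in one arm only.

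**3. Outcomes against the 16-week score.**

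- Birth weight, gestational age and APGAR (Delivery Summary Sheet) are fixed at delivery. The stigma score follows by about 16 weeks.
- Antenatal adherence is a count of clinic visits. Table 1 records it at follow-up too, but the visits end by delivery. The stigma score follows the last visit by 16 weeks or more.
- Psychosocial scales are taken at the same visit, and the ACTG questionnaire covers the four days before it. The measurements are concurrent and order is not established.
- Infant mortality, hospitalizations and vaccinations accrue from birth up to that visit. They overlap with or precede the stigma score.
- CD4 count and viral load come from clinical records, and the HIV metrics section says that test dates need not match a study time point. Order is unknown and may differ between women.

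**4. Illustration (all parameters assumed).** Let A be arm (0 or 1). Stigma in pregnancy, M1, has variance 1 and does not depend on arm. The birth outcome is Y = 0.5A + e, with variance of e equal to 1. Stigma at 16 weeks is M2 = 0.5·M1 − g·Y + u, with variance of u equal to 1. The true indirect effect through stigma in pregnancy is zero. With M2 as the mediator:

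- Arm to mediator: a = −0.5g.
- Mediator to outcome, given arm: b = −g / (0.25 + g² + 1) = −g / (1.25 + g²).
- Apparent indirect effect: a·b = 0.5g² / (1.25 + g²). As a share of the total effect of 0.5, this is g² / (1.25 + g²).

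| g | a·b | Share of total effect |
|---|---|---|
| 0 | 0 | 0% |
| 0.2 | 0.02 / 1.29 = 0.016 | 3% |
| 0.4 | 0.08 / 1.41 = 0.057 | 11% |
| 0.6 | 0.18 / 1.61 = 0.112 | 22% |

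A simulation of 200,000 women with 3:1 allocation gave 0.000, 0.017, 0.057 and 0.114 (0%, 3%, 11% and 23%), which agrees within simulation error. With M1 as the mediator it gave 0.0 throughout.

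**The case against.** The strongest reply is that the models are called exploratory, the infant outcomes are stated to be unpowered, and the study is a pilot. The planned between-arm comparisons do not depend on mediation. An article may also leave the choice of mediator time point to an analysis plan. All of this limits the weight of the point. It does not remove it: an analysis plan can choose among measured time points, but it cannot supply a TAU score that the schedule excludes.

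A second reply is that the Introduction expects reduced stigma to persist postpartum and help sustain ART adherence, so stigma at 16 weeks is relevant to that part of the mechanism. This stands. For those outcomes the weakness is the ordinary one of measuring mediator and outcome together, not reversed order.

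A reader might also draw stronger conclusions that the documents do not support:

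- That the mediation analysis cannot be done. The regressions can be fitted with the 16-week score. What fails is their reading as mediation for antenatal and birth outcomes.
- That mediator and outcome coincide exactly for everything else. Infant events accrue over the 16 weeks, and CD4 and viral load dates vary.
- That the focus on early change predicting later change is presented as mediation. The plan speaks of prediction, and Table 1 already labels the comparisons involving the post-intervention score as within the intervention group. The limit is only left unstated at that sentence.
- That "We measure primary and secondary outcomes at three time points" in the Introduction is an error of substance. The Comparator and Assessments sections make clear that the middle time point is for MME women only.

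**Conclusion.** The point holds as a limit on interpretation. For antenatal visits, birth weight, gestational age and APGAR, no TAU woman has a stigma score between baseline and delivery. The only shared post-assignment score follows the outcome by about 16 weeks (16 or more for antenatal visits), so a fitted indirect effect cannot be called mediation. For outcomes taken at the 16-week visit or accruing up to it, order is not established, which is milder.

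The schedule finding rests on Table 1 and the sections cited, without outside assumptions. The size of a false indirect effect is not known. The range of 0% to about 22% depends wholly on the assumed parameters and shows only that the error could be anything from nothing to a visible share. Because the analyses are exploratory and the between-arm comparisons do not use the mediator, the severity is modest.

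**What to change.** In the Statistical analysis section:

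- Remove mediation by stigma for antenatal adherence and birth outcomes.
- For 16-week outcomes, report the association of stigma change with the outcome, adjusted for arm and for the outcome's baseline value where one was measured. Make no mediation claim.
- State that the analysis of baseline-to-post-intervention change as a predictor of follow-up is a within-MME association with no arm contrast.

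The mediation wording in the abstract can stay as a hypothesis, provided that the analysis does not claim to test it for antenatal or birth outcomes. The cost is wording only, with no new data and no change to the between-arm comparisons. The downside is that the pilot makes a smaller claim about mechanism.
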